### 2.5.3 HPV Type-Specific Replacement Measurements

**External Genital Warts or Cervical Dysplasia related to a specific non-vaccine HPV Type:**

A subject will be considered to have a case of external genital warts or cervical dysplasia related to a specific non-vaccine HPV type during the follow-up period if she has the following:

- On an individual biopsy or excised tissue, a consensus by the Independent Pathology Panel diagnosis of condyloma acuminata (genital warts), or on an individual biopsy, ECC, LEEP, or Conization (cold knife/laser) specimen a consensus by the Independent Pathology Panel diagnosis of CIN 1, CIN 2, CIN 3, cervical adenocarcinoma in situ (AIS), or cervical cancer

AND

- Detection of the relevant (from any of HPV types 31, 33, 35, 39, 45, 51, 52, 56, 58, or 59) HPV type by Thinsection PCR in an adjacent section from the same tissue block.

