Slides of wart/lesion biopsy or vaginal biopsy specimens will be prepared at the central pathology laboratory and reviewed by a pathologist for the purpose of management of the subject. The slides prepared from the genital wart/lesion biopsy (external and vaginal), as well as the investigator’s observation of whether the lesion is single or there are multiple lesions, will be submitted to the Independent Pathology Panel which will provide the final diagnosis for study purposes. The slides will be returned to the originating central pathology laboratory at the completion of review by the panel.

If the diagnosis of the Independent Pathology Panel is VIN 3/VaIN 3 or worse, and the diagnosis of the central laboratory is of lower grade abnormality, then the investigator will be notified of the discrepant diagnoses. The Independent Pathology Panel will be blinded to the results of the PCR analysis of the biopsy.

External genital and vaginal biopsy specimens will be sent to the SPONSOR's designee for HPV analysis. HPV analysiswill be performed on Thinsection microtomy specimens. Each biopsy specimen will be analyzed by HPV PCR, regardless of whether an HPV-related histologic diagnosis is made, for the purpose of determining the causal HPV type in the lesion. HPV typing will be performed using Multiplex PCR Assay to detect vaccine HPV types. Samples that test negative for HPV vaccine types will be analyzed for non-vaccine HPV types using type-specific PCR for multiple high-risk HPV types. The interval between the genital wart/lesion biopsy and the next scheduled study visit that includes a complete gynecological examination must be ≥2 months.

Treatment for VIN, VaIN, and genital warts is per the investigational site’s standards and practices. During genital wart treatment, follow-up biopsies should be obtained if new HPV-related lesions of differing morphology, and/or differing location appear. A recurrence of a lesion is defined as the reappearance within 2 months of a lesion of similar morphology in the same anatomical location after complete resolution of the initial lesion. Recurring lesions will not be biopsied. Otherwise, all new lesions will be biopsied.

**A subject with an external genital lesion that is histologically confirmed to be HPV-related (e.g., VIN, VaIN, and genital warts) by the SPONSOR central laboratory is to be referred to colposcopy.**

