If no lesion is noted on colposcopy and/or the colposcopy exam is unsatisfactory, and the subject was referred based on cytologic abnormality, an endocervical curettage (ECC) along with a careful inspection of the vagina may be performed if it is deemed by the investigator to be medically indicated. A curet may be used, but not a brush when obtaining the specimen. Thinsection HPV PCR analysis will be done on all ECC specimens, along with a histopathologic review. Additional Pap testing during the unscheduled colposcopy study visit is not allowed.

HPV analysis will be performed on biopsy tissue and Thinsection microtomy specimens. Each biopsy specimen will be analyzed by HPV PCR, regardless of whether an HPV-related histologic diagnosis is made, for the purpose of determining the causal HPV type in the lesion. HPV typing will be performed using Multiplex PCR Assay to detect vaccine HPV types on all samples. Samples will be analyzed for non-vaccine HPV types using Type-Specific PCR for High-Risk HPV Types, specifically HPV types HPV 31/33/35/39/45/51/52/56/58/59.

Subjects who undergo cervical biopsy during the study may remain in the study. The interval between the cervical biopsy and the next scheduled visit that includes a pelvic exam must be at least 2 months.

Please refer to the Specimen Collection Procedures Manual for step-by-step procedures for cervical biopsy and endocervical curettage collection and handling.

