***Referral for Definitive Therapy***

Subjects who undergo cervical biopsy during the study will be referred for definitive therapy according to mandatory protocol prescribed guidelines including:

- Biopsy-confirmed CIN 2, CIN 3, or cervical cancer
- Two repeat HSIL diagnoses (regardless of whether they are consecutive or not) on ThinPrep™ Pap test without confirmed CIN 2, CIN 3, or cervical cancer on biopsy or ECC
- An ECC demonstrating CIN 2, CIN 3, AIS, or cervical cancer
- A single HSIL Pap with an unsatisfactory colposcopic examination including a negative examination of the vagina and a negative ECC
- Atypical Glandular Cells or AIS on Pap result with unsatisfactory colposcopy or negative biopsy or ECC; or

Flow charts illustrating these indications for definitive therapy is provided in Section 7 (Attachments).

Cervical tissue specimens will be submitted to the central laboratory selected by the SPONSOR for histopathologic review. In addition, specimens will be prepared by the central lab for HPV PCR analysis by the SPONSOR or its designee using the Multiplex PCR Assay to detect vaccine and non-vaccine HPV types on all samples.

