### 3.3.4 PCR Assays to Detect HPV in Clinical Specimens

All TS microtomy biopsy specimens will be tested for detection of HPV types 6, 11, 16, 18, 31, 33, 35, 39, 45, 51, 52, 56, 58, and 59. HPV types 6, 11, 16, 18, 31, 33, 45, 52, and 58 will be analyzed by type-specific multiplex (L1, E6, E7 gene detection) PCR assay (described in Section 3.3.4.1). HPV types 35, 39, 51, 56, and 59 will be analyzed by the duplex (E6, E7 gene detection) PCR assay (using the preparation method described in Section 3.3.4.1).

Upon HPV type identification of the biopsy thin-sections, and case assignment via positive consensus of histology diagnosis and HPV PCR, the cases will be reviewed for HPV type mixed-infections which will be noted. Exploratory studies of these HPV type mixed-infection tissues may be conducted. Additional thin sections will be required and adjudication of the proximal sections by thin section HPV multiplex PCR will be conducted. Briefly, additional 4-5 micrometer sections of the mixed-infection tissue paraffin blocks will be cut using a fresh disposable blade per block and applying the standard procedures implemented to ensure no contamination in thin sections processing for PCR. Seven sections will be cut. The first two and last two will be individually placed in tubes (tube 1, 2, 6 and 7) and tested by HPV Multiplex PCR to confirm the mixed-type status in the book-end sections of this second, deeper cut in the paraffin tissue block. The middle three sections will be applied to membrane-coated slides with diluted tissue adhesive (TA, Diagnostic Products Corp.) and stained with hematoxylin and eosin (HE). The margins of the cancerous cell populations will be microscopically defined by the pathologists, photographed and Laser Microdissection of Cells (LMC) performed [3]. The dissected cell clusters will be collected, DNA extracted and HPV Multiplex PCR tested. All three sections 3, 4 and 5 will be individually analyzed and tested.

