### 3.3.5 PCR Assays to Detect HPV in Thinsections of Biopsy Tissue

PCR assays to determine HPV in biopsy Thinsections will be performed at a central laboratory designated by the SPONSOR. Thinsections are prepared for PCR using a DNA purification method (Qiagen Technology Kit). HPV 6, 11, 16, and 18 Multiplex PCR (see Section 3.3.4.1) will then be performed on a fraction of the DNA prepared from each Thinsection to determine the HPV type in the Thinsection. Thinsections positive by HPV multiplex PCR for HPV 6, 11, 16, and 18 may be further analyzed by HPV type-specific primers based on the HPV E7 genes only to quantify viral load (see above). Thinsections will also be further analyzed by type-specific multiplex or duplex PCR assays for additional HPV Types including 31, 33, 35, 39, 45, 51, 52, 56, 58, and 59. For description of these assays, see Section 3.3.4.1.

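### Genital and vaginal biopsies are typed for non-vaccine HPV conditionally in one section and unconditionally elsewhere; the conditional rule undercounts non-vaccine-type warts in the Section 2.5.3 endpoint

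*Protocol*

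**What the plan says.** The protocol gives typing rules for biopsies in several places.

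- **Genital Wart/Lesion Biopsy (in 3.2.3.3.7.3).** The rule covers this material: "External genital and vaginal biopsy specimens will be sent to the SPONSOR's designee for HPV analysis". Vaccine types are tested first. Then: "Samples that test negative for HPV vaccine types will be analyzed for non-vaccine HPV types using type-specific PCR for multiple high-risk HPV types".
- **Section 3.3.4.** "All TS microtomy biopsy specimens will be tested for detection of HPV types 6, 11, 16, 18, 31, 33, 35, 39, 45", with the list continuing to 59, which makes 14 types in all. Cases are then to be reviewed for mixed-type infection, and any found is to be noted.
- **Section 3.3.5.** "Thinsections will also be further analyzed by type-specific multiplex or duplex PCR assays for additional HPV Types including 31, 33" and the rest of the ten. No negative vaccine-type result is required. Section 3.3.4.1 also sets no such condition.
- **Cervical Biopsy and Endocervical Curettage (in 3.2.3.3.7.3).** "Samples will be analyzed for non-vaccine HPV types using Type-Specific PCR for High-Risk HPV Types", again without a condition.
- **Referral for Definitive Therapy (in 3.2.3.3.7.3).** Specimens are analysed "using the Multiplex PCR Assay to detect vaccine and non-vaccine HPV types on all samples".

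The replacement endpoint in Section 2.5.3 pools condyloma and cervical lesions of CIN 1 or worse. Its virological criterion is "Detection of the relevant (from any of HPV types 31, 33, 35, 39, 45, 51, 52, 56, 58, or 59) HPV type by Thinsection PCR". Detection of a vaccine type in the same tissue does not exclude the case.

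**The concern.** A laboratory cannot follow both the genital-biopsy sentence and Section 3.3.4. If it follows the former, a wart that is positive for HPV 6 and also carries HPV 51 stops at the vaccine-type result and is never tested for HPV 51. Section 2.5.3 would count that wart; the testing rule prevents it from being found.

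Three things are at stake:

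- Non-vaccine types are undercounted in co-infected warts.
- One composite endpoint is ascertained by two different rules, depending on the anatomical site of the biopsy.
- Vaccine/non-vaccine mixed infections in genital lesions go unseen, although Section 3.3.4 asks for mixed infections to be noted and Section 2.1.3 uses the frequency of multiple-type infection as an argument that replacement is unlikely.

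Section 3.5 says that no separate SAP will be issued for this follow-up, so the protocol itself is where the rule has to be settled.

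**Working it through.** The plan states no figure for this point, so the check is mainly a reading of the rules against each other.

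**Step 1: which lesions can become non-vaccine-type cases.**

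| PCR content of lesion | Counts under 2.5.3? | Found in a cervical specimen? | Found in a wart, conditional rule? | Found in a wart, 3.3.4 rule? |
| --- | --- | --- | --- | --- |
| Non-vaccine type only | Yes | Yes | Yes | Yes |
| Vaccine and non-vaccine type | Yes | Yes | No | Yes |
| Vaccine type only | No | No | No | No |

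The rules differ in the second row, and only for warts. VIN and VaIN are biopsied under the same genital rule but are not part of the 2.5.3 definition. CIN 2+ comes from cervical specimens, so the replacement comparison in Section 3.5.5.2 (CIN 2+ against an external Bogota cohort) is untouched.

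**Step 2: size, as an illustration only.** Let q be the share of vaccine-type-positive genital lesions that also carry one of the ten non-vaccine types. The protocol does not give q, so it is an assumption with range 0 to 1. Then

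hidden cases = q × (vaccine-type-positive genital lesions).

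The nearest counts are in Table 3-6: HPV 6/11-related external genital lesions, Colombia cohort, full analysis set, base study to Year 4. There were 3 cases (0.39%) with GARDASIL and 7 (0.90%) with placebo, which implies denominators of about 3/0.0039 = 769 and 7/0.0090 = 778.

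| q | GARDASIL, 3q | Placebo, 7q |
| --- | --- | --- |
| 0.10 | 0.3 | 0.7 |
| 0.25 | 0.75 | 1.75 |
| 0.50 | 1.5 | 3.5 |
| 1 | 3 | 7 |

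Under the Section 3.3.4 rule the hidden number is 0 for every q.

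These counts are a rough guide. They come from the base study, not the follow-up. External genital lesions are a wider class than condyloma. Genital lesions positive for HPV 16 or 18 are not tabulated separately and could add to the total. A woman with a masked wart may still be a case through another lesion.

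**Step 3: direction of bias if base-study rates are used as context.** Assume 10 true non-vaccine-type wart cases in each group, the Table 3-6 masking counts, and q = 0.25.

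- Both periods typed conditionally: vaccinated 10 − 0.75 = 9.25, base-study placebo 10 − 1.75 = 8.25, ratio 1.12.
- Base study typed in full, follow-up typed conditionally: 9.25 against 10, ratio 0.93.

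For q from 0.1 to 0.5 the first ratio runs from 1.04 to 1.31 and the second from 0.97 to 0.85. The true ratio is 1 throughout. The sign therefore depends on the base-study typing rule. Section 1.2 says that specimens are tested as in the base study, but the protocol does not describe how base-study genital lesions were typed.

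**The case against.** The strongest defence is that the genital-biopsy sentence does not contain the word *only*, and that Section 3.3.4 is where the assays are specified. If the laboratory works from Section 3.3.4, nothing is hidden. That is right as far as it goes: the harm depends on which section is followed. But the condition has no function if every sample is typed anyway, and the parallel cervical text omits it. The two rules still have to be reconciled.

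A second defence is that Section 2.1.3 speaks of disease not related to HPV 6/11/16/18, which might mean lesions free of vaccine types. Section 2.5.3 does not say so, and Sections 3.3.1 and 3.5.3 make it the governing definition. Even on that reading, the exclusion would have to be written down and applied to cervical lesions too.

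A third is that the Colombian per-protocol GARDASIL group had no HPV 6/11 external genital lesions by Year 4, so little would be masked in Cohort 1's primary population. That supports a small effect. It does not remove it, because the conditional rule acts on the lesion's PCR result whatever the woman's type-specific eligibility, and Cohort 2 is analysed in the full analysis set.

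In the other direction, a reader might infer that the rule builds a false replacement signal into the endpoint: vaccination clears vaccine types, more lesions become eligible for further typing, and non-vaccine detection rises. The documents do not support that. Everyone in the follow-up is vaccinated (Section 3.2.3.4). The only replacement comparison specified is cervical CIN 2+. The base-study comparisons in Section 3.5.5.1 are framed around vaccine-type disease. Only the general statement in Section 2.7 about putting incidence in context could reach this endpoint, and Step 3 of the working shows that the bias could then run either way.

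**Conclusion.** The contradiction is real. Followed as written, the genital-biopsy rule undercounts non-vaccine types in co-infected warts, hides vaccine/non-vaccine mixed infections in genital lesions, and leaves the Section 2.5.3 composite resting on two ascertainment rules. This is an error in a stated rule, not a missing detail.

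Its reach is limited to the wart component. No hypothesis is tested. Base-study counts suggest at most a handful of cases, but the co-infection share is an assumption and the follow-up lesion count is unknown, so the documents do not fix the number. The certain effect is undercounting; neither a spurious rise nor a masked rise in non-vaccine types can be claimed from what is shown.

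**What to change.** Replace the conditional sentence under Genital Wart/Lesion Biopsy with the Section 3.3.4 rule: every external genital and vaginal thinsection is tested for all 14 types, whatever the vaccine-type result.

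If non-vaccine-type wart incidence is to be set against base-study rates, state how base-study genital lesions were typed and make that comparison only where the rules match.

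The cost is one amended sentence, one added statement on base-study typing and probably few extra PCR runs. Section 3.3.4 already commits the study to the tests.

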***Cervical Biopsy and Endocervical Curettage***

If cervical biopsies and/or endocervical curettage (ECC) specimens are obtained, specimens must be sent to the central laboratory designated by the SPONSOR for analysis. This unscheduled visit(s) will be considered part of the study and any specimens collected will be handled in a protocol-specified manner.

Slides of cervical biopsy/ECC specimens will be prepared at the central laboratory selected by the SPONSOR and reviewed by a pathologist for the purpose of management of the subject. The slides will subsequently be reviewed by the Independent Pathology Panel for consensus diagnosis. The slides will be returned to the originating central pathology laboratory at the completion of review by the panel.

The investigator will be notified of any histologic diagnosis made by the Independent Pathology Panel that is more severe than the one made by the central laboratory pathologist. For the purposes of this protocol, the SPONSOR and the central laboratory have defined a discordant diagnosis as a case in which the Thin Prep™ Pap test is more severe than the subsequent cervical biopsy (and ECC, if obtained) diagnosis and the Pap test diagnosis would ultimately lead to definitive therapy. If the Pap diagnosis is AGC, AIS, ASC-H or LSIL, cannot exclude HSIL and the biopsy diagnosis is CIN 1 or less, then this is defined as discordant. The investigator will be notified of all discordant diagnoses. A discordant diagnosis will require a review of the results. If upon review the results are amended, the triage algorithm should be followed (if the Pap results are amended, i.e., not HSIL, not AGC, not ASC-H, then follow the routine visit schedule, or if the biopsy results are amended to show CIN 2/3 or worse, proceed to definitive therapy). If the discordant results are reviewed but not amended, a repeat Pap and a colposcopy/ECC are required (≥2 months after the last colposcopy/ECC). If the diagnosis of the pathology panel is CIN 2/3 or worse, and the diagnosis of the central laboratory is of a lower grade abnormality, then this is defined as a safety net case. Safety net notification does not require a review of the results.

If no lesion is noted on colposcopy and/or the colposcopy exam is unsatisfactory, and the subject was referred based on cytologic abnormality, an endocervical curettage (ECC) along with a careful inspection of the vagina may be performed if it is deemed by the investigator to be medically indicated. A curet may be used, but not a brush when obtaining the specimen. Thinsection HPV PCR analysis will be done on all ECC specimens, along with a histopathologic review. Additional Pap testing during the unscheduled colposcopy study visit is not allowed.

HPV analysis will be performed on biopsy tissue and Thinsection microtomy specimens. Each biopsy specimen will be analyzed by HPV PCR, regardless of whether an HPV-related histologic diagnosis is made, for the purpose of determining the causal HPV type in the lesion. HPV typing will be performed using Multiplex PCR Assay to detect vaccine HPV types on all samples. Samples will be analyzed for non-vaccine HPV types using Type-Specific PCR for High-Risk HPV Types, specifically HPV types HPV 31/33/35/39/45/51/52/56/58/59.

Subjects who undergo cervical biopsy during the study may remain in the study. The interval between the cervical biopsy and the next scheduled visit that includes a pelvic exam must be at least 2 months.

Please refer to the Specimen Collection Procedures Manual for step-by-step procedures for cervical biopsy and endocervical curettage collection and handling.

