##### 3.2.3.3.7 Colposcopy/Biopsy/ Definitive Therapy Procedures

###### 3.2.3.3.7.1 Triage for Abnormal Pap Tests

Subjects with ThinPrep™ Pap tests obtained during the study showing abnormalities should be referred to colposcopy and biopsy according to the Mandatory Algorithm for Triage of Abnormal Pap tests to Colposcopy provided in Table 3-2. This is a protocol-prescribed strategy and any deviation will require prior approval by the SPONSOR. Colposcopy may also be performed in the case of an unresolved post-coital bleeding that persists after completion of appropriate work-up. Prior to a colposcopy for this indication, the case must be reviewed with the SPONSOR and a note to file must be generated.

If a subject is scheduled to undergo a hysterectomy, a colposcopy with biopsy should be performed.

Table 3-2

Mandatory Algorithm for Triage of Abnormal Pap Tests to Colposcopy

| ThinPrep™ Pap Result | Action |
| --- | --- |
| Negative for intraepithelial lesion or malignancy (includes reactive, reparative, inflammatory, etc.) | Routine visit interval as specified by the protocol. |
| Atypical Squamous Cells—Undetermined Significance (ASC-US) | Central laboratory performs reflex HPV testing on residual ThinPrep™ material (High Risk and Low Risk Probe, Hybrid Capture II, DIGENE™). If at least 1 probe is positive or if no result is obtained, the subject will be referred for colposcopy. If both probes are negative, then the subject will return for Pap screening at the routine visit interval. |
| Atypical Squamous Cells—cannot exclude HSIL (ASC-H) | Referral to colposcopy. |
| Low-grade Squamous Intraepithelial Lesion (LSIL) | Follow-up in 6 months |
| High-grade Squamous Intraepithelial Lesion (HSIL) | Referral to colposcopy. |
| Atypical Glandular Cells (to include atypical endocervical, endometrial, NOS; Adenocarcinoma in Situ, adenocarcinoma, etc.) | Referral to colposcopy. |
| Unsatisfactory | Repeat ThinPrep™ Pap test as soon as possible, but not less than 4 weeks from the Pap test that had the unsatisfactory finding. |
| Colposcopy should be performed according to the guidelines in this table or as indicated clinically over the ensuing period of follow-up.  Colposcopy must be performed within 2 months of the abnormal Pap result that required the referral to colposcopy. | |

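### The list of Pap results that count as discordant with a biopsy of CIN 1 or less omits HSIL, although the same paragraph twice treats HSIL as covered

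*Protocol*

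**What the plan says.** Under Cervical Biopsy and Endocervical Curettage in Protocol Section 3.2.3.3.7.3, one paragraph states the discordance rule in three ways.

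- **Definition.** The Pap must be more severe than the biopsy (and ECC, if taken), and "the Pap test diagnosis would ultimately lead to definitive therapy".
- **List.** "If the Pap diagnosis is AGC, AIS, ASC-H or LSIL, cannot exclude HSIL and the biopsy diagnosis is CIN 1 or less", the case is discordant.
- **Amended results.** After the review, "if the Pap results are amended, i.e., not HSIL, not AGC, not ASC-H, then follow the routine visit schedule".

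Two consequences attach to a discordant case. The results are reviewed, and "If the discordant results are reviewed but not amended, a repeat Pap and a colposcopy/ECC are required", at least 2 months after the last colposcopy or ECC.

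Referral for Definitive Therapy, in the same section, gives HSIL two routes to treatment without CIN 2 or worse on biopsy: "Two repeat HSIL diagnoses (regardless of whether they are consecutive or not"), and "A single HSIL Pap with an unsatisfactory colposcopic examination" together with a negative vaginal examination and a negative ECC.

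**The concern.** In the list, HSIL appears only inside the qualifier attached to LSIL. Results that merely fail to exclude HSIL are therefore named, while HSIL is not. No clinical reason is given for this, and the sentences on either side point the other way.

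The rule exists to catch a biopsy that may have missed a high-grade lesion. A site or laboratory working from the list alone would not flag the squamous Pap result for which that possibility is most pressing, and the mandated review and repeat would not follow. What is at stake is the timely management of an individual woman.

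**Working it through.** No arithmetic decides the contradiction, so the three statements are set side by side for HSIL and ASC-H.

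| Statement | HSIL with CIN 1 or less | ASC-H with CIN 1 or less |
| --- | --- | --- |
| Definition | Covered: more severe than the biopsy, with two HSIL routes to definitive therapy | More severe than the biopsy; the therapy criteria shown have no ASC-H entry, but that list may be incomplete |
| List | Not named | Named |
| Amended-result clause | Named first | Named |

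The amended-result clause says what to do once a review has removed an HSIL reading. That makes sense only if HSIL cases enter review. Two of the three statements therefore include HSIL, and the list is the outlier.

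**Does another rule supply the repeat?** Take HSIL, a satisfactory colposcopy and a biopsy of CIN 1 or less.

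1. Table 3-2 (Section 3.2.3.3.7.1) sends HSIL to colposcopy, within 2 months of the abnormal result. It names no later step for a biopsy of CIN 1 or less.
2. The single-HSIL route to therapy needs an unsatisfactory colposcopy, so it does not apply. The other HSIL route needs a second HSIL Pap.
3. That second Pap cannot be taken at the colposcopy visit: "Additional Pap testing during the unscheduled colposcopy study visit is not allowed".
4. The safety-net notification applies only when the pathology panel reads CIN 2/3 or worse and the central laboratory reads lower. It does not respond to a Pap and biopsy that disagree.

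Nothing in the text shown mandates a repeat Pap before the next scheduled visit.

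**Length of the gap.** Inputs: scheduled Paps at Years 6, 8 and 10 (Section 3.2.3.3.5), each visit with a window of ± 6 months (Section 1.7). Assumption: the HSIL Pap was taken at a scheduled visit.

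- Nominal: 8 − 6 = 10 − 8 = 2 years = 24 months.
- Shortest: 24 − 6 − 6 = 12 months.
- Longest: 24 + 6 + 6 = 36 months.
- HSIL at Year 10: no later scheduled visit.

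For ASC-H left unamended after review, the repeat Pap and colposcopy/ECC are due from 2 months after the last colposcopy or ECC.

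**The case against.** The strongest reply is that the definition governs. It comes immediately before the list, it fits HSIL, and the list is not worded as exhaustive. Read whole, the paragraph makes HSIL with CIN 1 or less discordant, with review and repeat. Harm needs someone to apply one sentence and ignore its neighbours. This stands, and it is why the gap is stated only for a literal reading of the list. It does not make the list correct: a site should not have to infer that HSIL belongs in a safety rule.

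Three further points stand as limits. The triage and therapy charts in Section 7 are not shown and may include HSIL, so it cannot be said that the list is the sole statement of the rule by Pap result. The definitive-therapy list is introduced as non-exhaustive and its last item ends on a dangling conjunction, so an entry may be missing from the text at hand. The Table 3-2 footnote allows colposcopy on clinical grounds at any time in follow-up.

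A reader might also infer from the Table 3-2 entry for LSIL, "Follow-up in 6 months", that even LSIL is followed sooner than HSIL. The comparison does not work. LSIL waits those 6 months in place of immediate colposcopy, whereas the woman with HSIL has already been sent to colposcopy.

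**Conclusion.** The point holds as an internal contradiction, and the list is wrong as written. Its size is a gap in mandated follow-up for one group: HSIL, satisfactory colposcopy, biopsy of CIN 1 or less. Under the list the next mandated Pap is nominally 24 months away (12 to 36), with none after Year 10. Under the definition, a case left unamended has a repeat from 2 months. This assumes that the list is applied literally and that the unseen charts do not correct it. It is a gap in the mandatory rule and not a bar to care. The number of women affected cannot be computed from the Protocol.

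A reader might go further and infer that CIN 2+ cases would be missed and the long-term incidence biased downwards, given how few cases Section 2.7 expects. The documents do not support that. They identify no endpoint that would be lost. A lesion found at a later scheduled visit still counts in that analysis, and only an HSIL Pap at Year 10 has no scheduled visit after it. The effect of a single case on the person-year rates in Table 2-1 would be the same whatever its cause, and Section 3.5.5.1 makes life-table cumulative incidence the primary metric instead. No effect on the effectiveness estimates is demonstrated.

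**What to change.** Change the list to read: HSIL, AGC, AIS, ASC-H, or LSIL cannot exclude HSIL. Use the same list in the amended-result clause, which at present names only HSIL, AGC and ASC-H. Check both against the Section 7 triage and therapy charts before release, so that text and charts agree.

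The cost is one added term in the list, a matching edit in the next clause, and a letter to the site and central laboratory. The Summary of Changes shows that a clarification letter followed by an amendment has already been used in this study. HSIL cases left unamended would have the repeat Pap and colposcopy/ECC that the definition already implies. Sample size and analysis are unchanged.

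### The discordant-diagnosis paragraph sends a Pap amended to LSIL, or to unsatisfactory, back to routine visits, against the mandatory triage table

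*Protocol*

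**What the plan says.** Two parts of the Protocol apply.

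**Cervical Biopsy and Endocervical Curettage (within 3.2.3.3.7.3).** This paragraph covers women whose Pap is more severe than the biopsy that followed. A discordant pair must be reviewed. The general instruction is: "If upon review the results are amended, the triage algorithm should be followed". A parenthesis then explains it in two parts. The Pap part is "if the Pap results are amended, i.e., not HSIL, not AGC, not ASC-H, then follow the routine visit schedule". The other part sends a biopsy amended to CIN 2/3 or worse to definitive therapy. For the remaining case the text says: "If the discordant results are reviewed but not amended, a repeat Pap and a colposcopy/ECC are required".

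**Section 3.2.3.3.7.1, Table 3-2.** This is the mandatory algorithm, and of it the section says: "This is a protocol-prescribed strategy and any deviation will require prior approval by the SPONSOR". The LSIL row reads "Low-grade Squamous Intraepithelial Lesion (LSIL) | Follow-up in 6 months". The action for an unsatisfactory sample is: "Repeat ThinPrep™ Pap test as soon as possible, but not less than 4 weeks from the Pap test that had the unsatisfactory finding". For ASC-US the table orders reflex HPV testing, and then: "If at least 1 probe is positive or if no result is obtained, the subject will be referred for colposcopy". The routine visit interval is given only to a negative Pap and to ASC-US with both probes negative.

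Routine visits with a Pap are at Years 6, 8 and 10, each with a window of ±6 months (Study Flow Chart, 1.7).

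**The concern.** The general instruction and its explanation disagree. The parenthesis is offered as what following the algorithm means for an amended Pap, yet it reduces the table to one question: is the result still HSIL, AGC or ASC-H? If not, the woman returns to routine visits. The table draws finer distinctions. In particular it treats 6-month follow-up and the routine interval as separate actions, so the first cannot be read into the second.

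What is at stake is participant follow-up. A site coordinator is likely to act on the concrete wording in the parenthesis. Doing so for an amended LSIL or unsatisfactory Pap departs from a table whose deviations need the sponsor's prior approval, and the woman is seen later than the table intends.

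**Working it through.** No figure in the plan depends on this point, so the check sets the two texts side by side and then counts months.

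**Step 1: which results the parenthesis covers.** Table 3-2 has 7 result rows: negative, ASC-US, ASC-H, LSIL, HSIL, atypical glandular cells (AGC) and unsatisfactory. Removing the three that the parenthesis names leaves 7 − 3 = 4 rows. ASC-US splits by probe result, which makes 5 outcomes.

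**Step 2: compare the actions.**

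| Amended Pap | Parenthesis | Table 3-2 | Agree? |
| --- | --- | --- | --- |
| Negative | Routine | Routine | Yes |
| ASC-US, both probes negative | Routine | Routine | Yes |
| ASC-US, a probe positive or no result | Routine | Colposcopy | No, in wording only |
| LSIL | Routine | 6-month follow-up | No |
| Unsatisfactory | Routine | Repeat Pap, from 4 weeks | No |

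Three of the five differ in wording. In the ASC-US row the table's action is referral to colposcopy, and every woman in this paragraph has just had one. That leaves two with practical content: LSIL first, then unsatisfactory.

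**Step 3: does the earlier colposcopy visit cover those two?** For an unsatisfactory Pap it does not: the same section does not allow an additional Pap at the unscheduled colposcopy visit. For LSIL it gives partial cover. Colposcopy is due within 2 months of the abnormal Pap result, so a closer examination has taken place, but it is not the 6-month follow-up.

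**Step 4: timing.** Inputs are the visit years and window from 1.7 and the 6 months from Table 3-2, all counted from the Pap.

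- Nominal gap: Year 8 − Year 6 = 24 months (the same for Year 10 − Year 8).
- Shortest gap (first visit late, next visit early): 24 − 6 − 6 = 12 months.
- Longest gap (first visit early, next visit late): 24 + 6 + 6 = 36 months.
- Delay against the LSIL rule: 24 − 6 = 18 months nominal, from 12 − 6 = 6 to 36 − 6 = 30 months.
- After a Year 10 Pap there is no later routine visit, so the parenthesis leads to no study follow-up.

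These are gaps from the Pap, not delays from the amendment. The document sets no time limit for the review, so the delay from the amendment cannot be derived.

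**The case against.** The strongest defence is that this is a rule for after colposcopy. Table 3-2 decides who goes to colposcopy, whereas the paragraph applies once colposcopy and biopsy are done and the biopsy shows CIN 1 or less. The paragraph also contains actions that Table 3-2 lacks: definitive therapy, and the repeat Pap with colposcopy/ECC when nothing is amended. Its algorithm may therefore be wider than the table, and the attached investigator aids on triage and definitive therapy, which are not shown, may spell it out.

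Part of this stands. The algorithm probably does extend beyond Table 3-2, and the earlier colposcopy lowers the clinical stakes. But the parenthesis is presented as what the algorithm requires, not as an exception, and nothing in the protocol exempts biopsied women from Table 3-2. An attachment that is not shown cannot be assumed to resolve the conflict.

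It is also fair that the LSIL row does not say what the 6-month follow-up consists of, and that the table's footer allows colposcopy when clinically indicated. Both soften the consequence. Neither removes the conflict.

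A reader might infer three stronger points that the documents do not support:

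- **Probe-positive ASC-US as an equal conflict.** The required colposcopy has already been done.
- **Routine visits for LSIL that cannot exclude HSIL.** Such a result is not clearly outside HSIL, and the paragraph's own definition, "If the Pap diagnosis is AGC, AIS, ASC-H or LSIL, cannot exclude HSIL and the biopsy diagnosis is CIN 1 or less", makes it discordant.
- **Plain HSIL dropped because that list omits it.** The general definition of discordance and the amendment clause already presuppose it.

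**Conclusion.** The Pap part of the parenthesis is wrong as written, and the point is minor. It contradicts mandatory Table 3-2 for a Pap amended to LSIL and, less commonly, for one amended to unsatisfactory. For LSIL the next study contact is nominally 18 months later than the table requires (6 to 30 months with the windows), and there is none within the study after Year 10. This assumes that a site follows the parenthesis rather than the general instruction, that both intervals run from the Pap, and that no clinically indicated visit comes in between.

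The number of women affected cannot be derived from the document and is probably small. A reader might infer that the incidence estimates are compromised. The documents give no basis for that, and no statistical figure changes.

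**What to change.** In Cervical Biopsy and Endocervical Curettage, replace the Pap part of the parenthesis with: *apply the Table 3-2 action for the amended Pap result*. Keep the clause on biopsies amended to CIN 2/3 or worse. Check that the attached investigator aids say the same.

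The cost is one line of wording and that check. No new procedure is added, because the Table 3-2 actions are already mandatory.
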